### Statistical Analysis

This study is designed to test the null hypothesis that the VBX device group will demonstrate a primary patency that is less than or equal to the BMS group at 1-year follow-up; versus the alternative hypothesis that the VBX device group will demonstrate a primary patency that is greater than the BMS at 1-year follow-up.

### Sample Size Considerations

This study is designed with the assumption that 1-year primary patency will be 88% and 70% for the VBX device group and BMS group, respectively. The study assumptions are based on the FLEX clinical study data and a recent meta-analysis of covered stents and BMS (both balloon-expandable and self-expanding) in patients with TASC II C and D lesions with a minimum of 12-month follow-up [11].

A total sample size of 244 patients would be required to account for a 20% loss to follow-up in order to demonstrate statistical significance (α=.05) at a power of 88%.

### Primary and Secondary End Point

The study analysis plan will include the following analysis populations: (1) intent-to-treat population (randomized patients categorized by assigned treatment); (2) as-treated population (randomized patients categorized by treatment received); and (3) per-protocol population. Primary patency at 1 year post implantation of the VBX device and BMS treatment groups will be analyzed with Kaplan-Meier estimates with separate estimates for each group. A 2-sided confidence interval of these estimates (α=.05) will be constructed to test the observed differences in primary patency rates between the treatment groups.

A comparative analysis of secondary end points will be performed. If the null hypothesis for the primary end point is rejected, key secondary end points will be evaluated for superiority using fixed sequential testing. In order, the secondary end points to be tested for superiority are cumulative target revascularization rate (first and recurrent events), the difference in mean ABI, and freedom from TLR.

Time-to-event secondary end points will be analyzed with Kaplan-Meier estimates with separate estimates for each group. Categorical end points for each treatment group will be analyzed with chi-square tests, and continuous end points for the treatment groups will be analyzed with 2-sample *t* tests.

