### End Points

The primary end point is 1-year primary patency and is defined as blood flow through the target lesion (no evidence of binary restenosis >50% or occlusion) without target lesion revascularization (TLR). Primary patency will be evaluated and adjudicated by the independent vascular Core laboratory. TLR events will be reviewed and adjudicated by the independent CEC (Table 1).

Secondary end points (defined in Table 1) will include technical success, acute procedural success, clinical success (through 30 days), changes in ABI (hemodynamic status), EQ-5D-5L, and walking impairment questionnaire through 5 years, and the following through 5 years: primary patency, freedom from binary restenosis, primary-assisted patency, secondary patency, freedom from TLR, cumulative reintervention rate (first and recurrent TLR), freedom from clinically-driven TLR, amputation-free survival, survival, and change in Rutherford category.

**Table 1 table1:** Study end point definitions.

Term	Definition
Primary patency	Blood flow through the target lesion (no evidence of binary restenosis >50% or occlusion) without a TLR^a^
Binary restenosis	Evidence of >50% restenosis or occlusion of the target lesions based on core laboratory adjudicated duplex ultrasound or angiography
Primary assisted patency	Blood flow maintained (no evidence of occlusion) through the target lesion with or without a TLR
Secondary patency	Blood flow through the target lesion with or without a TLR
Target lesion revascularization	Endovascular or surgical intervention performed on the target lesions
Clinically driven target lesion revascularization	Endovascular or surgical intervention performed on the target lesions in response to recurrent symptoms (increase ≥1 Rutherford category)
Amputation-free survival	Freedom from major amputation (target limb, amputation above the metatarsals) and all-cause mortality
Survival	Freedom from all-cause mortality
Technical success	Deployment of device with <30% residual stenosis on final angiography
Acute procedural success	Technical success and freedom from device or procedure-related SAE^b^ requiring intervention
Clinical success	Improvement from baseline of ≥1 Rutherford category and freedom from device or procedure-related SAE requiring intervention
Hemodynamic status	Change in ABI^c^ as compared to baseline
Rutherford category status	Change in Rutherford category as compared to baseline

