Quality of life assessments	Change in EQ-5D-5L responses as compared to baseline Change in WIQ^d^ responses as compared to baseline

^a^TLR: target lesion revascularization.

^b^SAE: serious adverse event.

^c^ABI: ankle-brachial index.

^d^WIQ: walking impairment questionnaire.

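### Unadjusted two-sample t tests for ABI (a key secondary in the fixed sequence), EQ-5D-5L and WIQ give up precision that the collected baseline values would supply

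*Protocol article*

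**What the plan says.** In the protocol article, the section Primary and Secondary End Point states that "continuous end points for the treatment groups will be analyzed with 2-sample" *t* tests. It names no covariate, and no baseline-adjusted model appears elsewhere in the article.

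The same section says that, once the primary null hypothesis is rejected, "key secondary end points will be evaluated for superiority using fixed sequential testing". Cumulative target revascularization comes first, followed by "the difference in mean ABI, and freedom from TLR".

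The End Points section lists as secondary end points "changes in ABI (hemodynamic status), EQ-5D-5L, and walking impairment questionnaire through 5 years". Table 1 defines hemodynamic status as ABI change relative to baseline. It defines quality of life in the same way: "Change in EQ-5D-5L responses as compared to baseline", with a matching entry for the WIQ.

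The only power statement, under Sample Size Considerations, concerns the primary end point. The article gives no SD, expected difference, correlation or power for ABI.

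**The concern.** Baseline ABI, EQ-5D-5L and WIQ must be measured for the end points in Table 1 to exist, yet the stated test does not use them as covariates. Two consequences follow.

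- **Precision.** In a randomized comparison, adjusting for the baseline value of the same measurement usually reduces the variance of the treatment effect at no cost in data. An unadjusted *t* test gives this up.
- **Two readings of the ABI test.** Table 1 points to change from baseline, while the sequence speaks of a difference in mean ABI. A *t* test on change and a *t* test on follow-up values can give different estimates and p values in the same data. They also respond to a chance baseline imbalance in opposite directions.

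What is at stake is mainly the ABI test. If the primary and the cumulative revascularization tests succeed but ABI fails, freedom from TLR cannot be claimed, whatever its own data show. EQ-5D-5L and WIQ are outside the sequence, so for them only the precision of the reported comparison is affected.

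**Working it through.** **1. The plan's own figure.** The article assumes that "1-year primary patency will be 88% and 70% for the VBX device group and BMS group, respectively", with 1:1 allocation, two-sided alpha 0.05 and 88% power. The pooled normal-approximation formula for two proportions gives 99 per arm, or 198 evaluable. Dividing by 0.80 for loss to follow-up gives 247.5, so 248, against the stated 244. Conversely, 244 × 0.80 = 195.2 evaluable, about 97.6 per arm, and power there is 87.6% (pooled variance) or 88.6% (unpooled). The stated design reproduces. It concerns the primary end point only, and nothing below changes it.

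**2. Variance of the three ABI analyses.** Let σ be the SD at baseline and at follow-up (assumed equal), ρ the correlation between them, and n the number per arm. The variance of the estimated treatment difference is (2σ²/n) times a factor:

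- *t* test on follow-up values: 1
- *t* test on change: 2(1 − ρ)
- ANCOVA on baseline: 1 − ρ²

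So ANCOVA/change = (1 − ρ²)/[2(1 − ρ)] = (1 + ρ)/2, and ANCOVA/follow-up = 1 − ρ². The article does not give ρ, so a range is assumed.

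| ρ (assumed) | ANCOVA / change-score *t* test | ANCOVA / follow-up *t* test |
|---|---|---|
| 0.3 | 0.65 | 0.91 |
| 0.5 | 0.75 | 0.75 |
| 0.7 | 0.85 | 0.51 |

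The two columns belong to alternative tests, and only one can apply. At ρ = 0.5 either *t* test needs 1/0.75 = 1.33 times the patients for the same precision.

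**3. What this means for power.** The article states no power for ABI. Suppose, for illustration, that the *t* test had 80%. Power with ANCOVA at the same n is Φ[(1.960 + 0.842)/√ratio − 1.960].

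- Against the change-score test: 93.5%, 89.9% and 86.0% at ρ = 0.3, 0.5 and 0.7.
- Against the follow-up test: 83.6%, 89.9% and 97.5%.

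**4. Chance baseline imbalance.** With about 97.5 evaluable per arm, the baseline difference has standard error √(2/97.5) = 0.143 SD, so a 95% range of ±1.96 × 0.143 = ±0.28 SD. Given an imbalance of 0.28 SD:

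- The follow-up comparison shifts by ρ × 0.28: 0.08, 0.14 and 0.20 SD at ρ = 0.3, 0.5 and 0.7.
- The change comparison shifts the other way by (1 − ρ) × 0.28: 0.20, 0.14 and 0.08 SD. It over-corrects.
- ANCOVA removes the expected shift in both cases.

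**5. Why ANCOVA settles change versus follow-up.** Write F for follow-up, B for baseline and T for treatment. If F = a + τT + βB, then F − B = a + τT + (β − 1)B. The treatment effect τ and its standard error are the same for either outcome.

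**6. If the SDs differ.** Let the baseline SD be k times the follow-up SD. The change-score factor is then 1 + k² − 2ρk, and its excess over 1 − ρ² is (k − ρ)², which is never negative. Unequal SDs change the size of the gain over the change-score test but not its direction; the gain vanishes only at k = ρ.

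**The case against.** The strongest reply is that nothing here is an error. Under 1:1 randomization an unadjusted *t* test is valid and unbiased over repeated randomizations. This stands: the cost is precision, and the shifts in step 4 are conditional on the imbalance that happens to occur.

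A reader might infer that the plan ignores baseline altogether and leaves any imbalance in the estimate. The article does not support that. On the Table 1 definition the tested quantity is change, which does use baseline. The remaining defect is that the coefficient is fixed at 1. Only a comparison of follow-up values would leave baseline unused.

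The mean ABI wording in the sequence may also be shorthand for the Table 1 end point, since no other ABI end point is defined. That is plausible, and on that reading only the change-score column applies, where the gain shrinks as ρ rises (15% of variance at 0.7). The shorthand is nevertheless unclear for a test in the sequence. ANCOVA settles change versus follow-up, but not the time point, nor the limb to be used in bilateral disease.

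The size is generic, because ρ and the equal SDs are assumed. This also stands. A reader might further infer that the ABI test is underpowered, but the article gives nothing from which to judge that.

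Finally, a reader might extend the point to change in Rutherford category, because "Categorical end points for each treatment group will be analyzed with chi-square tests". The article does not assign that end point to any test, and binary end points such as clinical success fit a chi-square test well. No criticism of the Rutherford analysis can rest on this text.

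**Conclusion.** The point holds as an avoidable inefficiency in a stated method, together with unclear wording at one step of the fixed sequence. It is not a validity problem. For ρ between 0.3 and 0.7 and equal SDs, baseline-adjusted ANCOVA would cut variance by 15% to 35% if the planned test is on change, or by 9% to 49% if it is on follow-up values. The true gain depends on a correlation that the article does not report.

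The main consequence lies with ABI, because it precedes freedom from TLR. It is conditional: the two tests ahead of ABI must succeed and ABI must fail. For EQ-5D-5L and WIQ the gain is in precision only, and treating them as continuous scores is an inference from the end point definitions. The analysis plan is not shown, but the *t* test is written into the article, so this is a choice already made and not a detail left open.

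**What to change.** Under Primary and Secondary End Point, replace the two-sample *t* test for ABI with ANCOVA of follow-up ABI on treatment and baseline ABI. Name this as the test in the fixed sequence, and state its time point and which limb's ABI is used when disease is bilateral. Use the same baseline-adjusted model for EQ-5D-5L and WIQ scores; a repeated-measures model over visits with baseline as covariate would also serve.

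Make the change before any unblinded comparison. It costs protocol and analysis-plan wording and minor analysis work. No additional data are needed, since the baseline values are already collected.

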### Trial Organization and Oversight

The Executive Steering Committee, consisting of multidisciplinary (vascular surgery, interventional cardiology, and interventional radiology) key opinion leaders, will provide study guidance and clinical oversight. The sponsor will provide study oversight in partnership with contract research organizations for database development, data monitoring, and independent review of study outcomes.

All imaging required by the study including duplex ultrasound and angiography, will be sent to the independent study core laboratory for centralized review and adjudication. An independent CEC will review and adjudicate potential end point–related events. For end point analysis, the sponsor will use data adjudicated by the core laboratory and CEC.

## Results

Site enrollment is currently in process, and participant enrollment is anticipated to begin in October of 2023. Participant enrollment is expected to take up to 32 months. Once all participants are enrolled, follow-up will continue through 5 years.

## Discussion

### Progressive Standards

The literature for long-term, randomized comparison studies for the treatment of AIOD is limited and, therefore, there are no accepted, published guidelines regarding the selection of either bare metal or covered stents. The COBEST trial [12] is the reference data often cited supporting the use of covered stents in complex AIOD. However, the trial was a noninferiority study with minimal statistical power, limited experience in 1 country, only an 18-month follow-up visit, and no independent core laboratory review for adjudication of end points. Furthermore, the COBEST trial was designed to evaluate binary restenosis rather than primary patency. The DISCOVER trial [13,14] failed to show any benefit of covered stents in “advanced” common iliac artery disease across all end points, likely due to the majority of TASC II A and B lesions. The FLEX trial included patients with tortuous iliac arteries, severe calcification, chronic total occlusions, and those who required kissing stents at the aortic bifurcation [7]. Importantly, despite the inclusion of more challenging iliac pathology, the FLEX study demonstrated a 1-year patency of 94.5% for the VBX stent-grafts in the treatment of AIOD involving the common or external iliac arteries [8]. The physician-initiated long-term follow-up of the FLEX study [23], demonstrated a 5-year patency of 89.5% which appears significantly greater than the 5-year patency of 74.7% for covered stents in the COBEST study [12]. While these studies suggest that the primary patency of covered stents may be better than BMS for the treatment of complex AIOD, there is a lack of level 1 evidence and no clear consensus regarding the optimal stent selection in AIOD.

The objective of the FORWARD study is to demonstrate the superiority of the VBX device for primary patency when compared to BMS in complex iliac occlusive disease in a prospective, multicenter, randomized controlled trial. The data from this study aims to provide level 1 evidence that will significantly enhance therapeutic decision-making and help establish a standard of care to guide clinical practice for patients with symptomatic severe aortoiliac disease. The FORWARD study is powered for superiority and includes only complex, unilateral, or bilateral lesions involving the common or external iliac arteries. To mirror real-world practice more closely, patients with minor tissue loss (Rutherford class 5) and patients requiring hemodialysis will be included. This study is a multidisciplinary endeavor involving vascular surgery, interventional cardiology, and radiology across multiple countries with a blinded core laboratory review of end points in hopes that the outcomes will be widely accepted by all parties that treat symptomatic patients with complex AIOD.

### Limitations

In the design of this study, multiple considerations were taken to curb the number of limitations. While the study intends to target complex diseases, the results may not be generalizable to populations with less complex diseases. This population is less frequent and may slow enrollment. The study is powered to demonstrate superiority at 1 year, however, longer-term outcomes are also clinically relevant. Additionally, due to the nature of the procedure, blinding of the implanting investigator is not possible which has the potential to induce bias.

## Appendix

Multimedia Appendix 1 CONSORT 2010 Checklist.

## Abbreviations

ABI: ankle-brachial index
AIOD: aortoiliac occlusive disease
BMS: bare metal stents
CEC: Clinical Events Committee
ISO: International Organization for Standardization
PAD: peripheral artery disease
TASC: Trans-Atlantic Inter-Society Consensus
TLR: target lesion revascularization
VBX device: GORE VIABAHN VBX Balloon Expandable Endoprosthesis
